**Additional exploratory mediating variables including the following:**

- Cognitive Appraisal scale will be used to measure how participants appraise the highly stressful events they have experienced, which has 13 items and good internal reliability ( $\alpha = 0.92$ ).
- Self-Compassion will be measured using the self-kindness subscale (5 items) and the mindfulness subscale (2 items) of the Self-Compassion Scale, which has good internal reliability ( $\alpha = 0.86$ ).
- Loneliness will be measured using the 3-item version of University of California, Los Angeles (UCLA)-Loneliness Scale, which has good internal reliability ( $\alpha = 0.88$ ).
- Cancer-related identity will be measured using a question, "When you think about yourself in relation to your cancer, how much does each of these phrases describe you?" (1) a victim of cancer, (2) a cancer patient, (3) a person who has had cancer, (4) a survivor, and (5) a person who recovered, each rated from 1 (not at all) to 5 (Very much).
- Intrusive Thoughts will be measured using the intrusion subscale of the Impact of Event Scale (IES)-6, which has 2 items and good internal reliability ( $\alpha = 0.80$ ).

**Mood check**

- Global Mood and Life Satisfaction Sliders. Mood will be measured with the Global Mood and Life Satisfaction Sliders. Participants are asked to rate their general affect ("How do you feel right now?") and life satisfaction (How satisfied with your life are you right now?). The scores range from 0-100 with a higher score indicating greater satisfaction.

#### Writing Manipulation Check

- Writing manipulation will be measured using 4 questions, "Overall, how personal were the essays that you wrote?", "Overall, how much did you reveal your emotions in what you wrote?", "Other than receiving monetary compensation, to what degree has this study been valuable or meaningful for you?", and "During the writing session, did you gain any new perspective of the disease." The scores range from 0 (not personal/not at all) to 6 (personal/a lot).
- Writing method (for participants who use REDCap for the writing tasks) will be assessed using two items, "Which method did you use for the writing tasks?" (1 = typing, 2 voice-to-text, 3. both typing and voice-to-text) and (answer if participant select 2 or 3) "In which writing session(s) do you use voice-to-text, or both typing and voice-to-text?" (Allows multiple choices; 1 = 1st writing task, 2 = 2nd writing task, 3 = 3rd writing task)

## 7.0 Data and Specimen Banking

**Power analysis.** Power analysis is based on testing hypotheses 1.1 in Aim 1 (primary aim) for the primary endpoints (QOL evaluated at 6 and 12 months) using nQuery 7.0. A sample size of 64 in each group (80 original, 20% attrition at 12 months, an assumption based on preliminary study 2) will have at least 80% power to detect a difference in mean QOL of 0.60 standard deviation (SD) using a two-sample *t*-test with a two-sided **0.0125 significance level (with a Bonferroni adjustment for the four primary comparisons)**. The *t*-test is appropriate to estimate power because the primary hypothesis is specified as contrasts at specific time points. The effect size of 0.60 was estimated from preliminary study 2, which compared expressive writing with the control at 6 months. For the same reason, we expect that the self-cultivation intervention condition will have an effect size of 0.6 at the follow-ups. The same sample size will have 80% power to detect a standardized effect size of 0.499 (a medium effect size) in between-group differences in cortisol slopes and perceived stress (hypothesis 1.2), to detect a standardized effect size of 0.251 of the interaction between acculturation and treatment conditions (hypothesis 2.1), and to detect a mediation effect (standardized coefficient of 0.35 in the *b* path and standardized between-group difference of 0.60) (hypothesis 3.1), with a 0.05 two-sided significance level.

**Quantitative data analysis.** Before we begin inferential procedures, we will conduct extensive descriptive analyses on the data collected. Distributional assumptions will be evaluated, and if indicated, normalizing (such as log) transformations or robust procedures will be used. Appropriate procedures to assess the validity and reliability of questionnaires will be used.

**Aim 1.** Given the longitudinal nature of the study, we will use linear mixed-effects models (LMMs) to assess the effects of the interventions on outcomes. Treatment condition and time will be included and tested in the model, as well as their interaction, with adjustment for covariates including the baseline outcome value, time since diagnosis, and disease stage. If needed, we will also control for potential confounders such as demographic or other clinical variables correlated with outcome variables. Potential heterogeneity across recruitment sites will be accounted for by adding site-specific random intercepts. The repeated-measures correlation structure will be selected based on the Bayesian information criterion (BIC). The primary outcome will be a composite scale of QOL based on the FACT-B total score. Hypothesis 1.1 (QOL at 6- and 12-month follow-ups for both intervention conditions) will be tested against the control condition within the LMMs based on appropriately constructed contrasts, each with a *two-sided 0.0125 level of significance, to ensure that the overall type I error rate across the four tests does not exceed 0.05. Controlling the overall type I error rate for testing the four primary hypotheses will help increase the reproducibility of our main study findings.*

All other analyses described below will use a two-sided significance level of 0.05 without adjustment for multiple testing. The corresponding results will thus be interpreted as hypothesis-

generating. The above LMMs will be repeated for medical appointments and perceived stress as outcomes (hypotheses 1.1 and 1.2). We will conduct linear regression analyses with stress biomarkers (cortisol and alpha-amylase) as the outcomes (hypothesis 1.2). The average levels and average slope of change in the 2 days at the 6-week follow-up will be used as the outcome of interest for each stress biomarker. We will control for potential confounding variables such as medical conditions and medications.

**Aim 2.** To characterize the moderation effect of acculturation/enculturation on the intervention (hypothesis 2.1), we will use LMMs like those in Aim 1 but test additional interaction effects between acculturation/enculturation subscale composite scores and intervention conditions. Items to assess the language aspects in the acculturation/enculturation subscales will also be explored as potential moderators. Furthermore, we will test interaction effects between intervention conditions and additional potential moderators (time since diagnosis, age, age of migration, , intervention delivery modes (receiving instructions via mail and writing by hand vs. receiving instructions and writing online), because the effects of the interventions may also depend on these factors. For example, those who are more recently diagnosed or more comfortable writing in Chinese may benefit more from the interventions.

**Aim 3.** To identify potential mechanisms by which the expressive writing intervention yields health benefits (hypothesis 3.1), we will conduct a longitudinal mediation analysis. Specifically, we will use measures of QOL outcomes at 6- and 12-month follow-ups and each of the potential mediators (posttraumatic growth, relationship harmony, and self-stigma) at 6-week and 6-month follow-ups, respectively, in the a and/or b paths of the mediation models (each path being a LMM). We will use bootstrapping in testing for the indirect effect of each mediator on QOL outcome. We will also explore multiple mediator models in case more than one mediator emerges.

**Missing data and dropouts.** The LMMs, as a likelihood-based regression method, will give valid (e.g., asymptotically unbiased) estimates of effects provided that the missingness probability depends only on the observed variables in the model (missing at random). However, data may not be missing at random; thus, we will conduct sensitivity analyses assuming different missing data mechanisms, especially when the attrition rate is moderate or high (e.g., >10%) and/or the attrition is unbalanced across intervention conditions. We will consider multiple imputation approaches based on relevant baseline participant characteristics to account for the missing-at-random mechanisms. We will also explore pattern-mixture and selection models to account for potential missing-not-at-random mechanisms.

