#### **4.0 Study Endpoints**

**The primary outcome will be QOL** at the 6 month and 12 month follow-ups and the secondary outcomes will be perceived stress, stress biomarkers, and medical appointments for cancer-related morbidities.

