Nearly all of the standardized questionnaires in the study have been validated in Chinese samples with good internal reliability. Questionnaires are provided in Appendix A. Table 1 shows the assessment schedule. Primary outcome, secondary outcomes, mediators, moderators, and clinical information (e.g., medical appointments, cancer recurrence, treatment type, cancer stage, time since diagnosis) will be self-reported at

| TABLE 1. Constructs, Measures, and Assessment Schedule |                 |                                                         |           |      |       |        |
|--------------------------------------------------------|-----------------|---------------------------------------------------------|-----------|------|-------|--------|
| Role                                                   | Construct       | Measures                                                | Base-line | 6 WK | 6 MTH | 12 MTH |
| Primary outcome                                        | Quality of life | Functional Assessment of Cancer Therapy-Breast (FACT-B) | x         |      | x     | x      |

2020-0708: Writing to Heal: A Culturally Based Brief Expressive Writing Intervention for Chinese Immigrant Breast Cancer Survivors

|                   |                           |                                                                  |                                                                                                             |   |   |   |   |
|-------------------|---------------------------|------------------------------------------------------------------|-------------------------------------------------------------------------------------------------------------|---|---|---|---|
| Secondary outcome |                           | Medical appointments for cancer-related morbidities  | Prospectively recorded medical appointments for non-routine cancer-related problems (e.g., breast symptoms) |   | x | x | x |
|                   |                           | Perceived stress                                                 | Perceived Stress Scale (PSS)                                                                                | x | x | x | x |
|                   |                           | Fear of cancer recurrence                                        | FACT21                                                                                                      | x | x | x | x |

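### With only two follow-up times for QOL, choosing the covariance by BIC can save one parameter at most and may move the time-specific contrasts slightly off 0.0125; prespecify unstructured for the primary model

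*Protocol*

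**What the plan says.** Section 7.0 (Quantitative data analysis, Aim 1) tests the primary hypothesis in a linear mixed model with condition, time and their interaction. On the covariance it gives one rule: "The repeated-measures correlation structure will be selected based on the Bayesian information criterion (BIC". It lists no candidate structures.

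The adjustment covariates are given as "including the baseline outcome value, time since diagnosis, and disease stage", so baseline QOL is a regressor and not a repeated response. The power paragraph refers to "primary endpoints (QOL evaluated at 6 and 12 months". The Table 1 row for the "Functional Assessment of Cancer Therapy-Breast (FACT-B" in section 6.0 has marks at baseline, 6 months and 12 months, and none at 6 weeks.

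Each of the four contrasts (two interventions against control, at two visits) is tested at a "two-sided 0.0125 level of significance, to ensure that the overall type I error rate across the four tests does not exceed 0.05". The power paragraph also states that the primary hypothesis is framed as contrasts at particular time points. The same models are reused for perceived stress and medical appointments, which Table 1 schedules at three follow-ups. Results outside the four primary contrasts are declared hypothesis-generating.

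**The concern.** Selecting a covariance structure has some purpose when there are many occasions and an unstructured matrix is costly. With two occasions it has almost none. Compound symmetry, AR(1) and Toeplitz are then the same two-parameter model (one variance, one correlation). Unstructured, heterogeneous compound symmetry and heterogeneous AR(1) are the same three-parameter model. Among these, BIC decides only whether the 6- and 12-month variances are made equal.

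Each primary contrast belongs to one visit and needs the variance at that visit. If the residual variances differ and the model pools them, the standard error is too small at the more variable visit and too large at the other. At stake are the stated per-contrast level and the width of the primary confidence intervals, in return for one saved parameter.

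**Working it through.** **Inputs from the protocol.** Three arms of 80, two-sided 0.0125 per contrast and four contrasts. For attrition: "A sample size of 64 in each group (80 original, 20% attrition at 12 months".

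**Inputs assumed.** The protocol does not give the ratio of the 12-month to the 6-month residual SD, r, or the residual correlation, ρ. The ranges used are r = 1.0 to 1.3 and ρ = 0.5 or 0.7. The assumed candidates are the equal-variance model and the unstructured model.

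**Step 1: the plan's own figures.** 80 × (1 − 0.20) = 64. 4 × 0.0125 = 0.05. A two-sample t-test with 64 per group, 0.60 SD and two-sided alpha 0.0125 has power 0.804 (exact noncentral t; 0.815 by normal approximation). The stated figure of at least 80% reproduces.

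**Step 2: how readily BIC pools.** Unstructured costs one extra parameter, so BIC keeps it only if the likelihood-ratio statistic exceeds log(240) = 5.48. With equal variances a chi-square on 1 df exceeds 5.48 with probability about 0.019, so BIC demands strong evidence before it separates the variances.

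**Step 3: level if pooling always happened.** With SDs 1 and r, the pooled SD is √((1 + r²)/2), and the true level of a nominal 0.0125 test is 2 × [1 − Φ(2.498 × pooled SD / true SD)]. For r = 1.1 the pooled SD is √1.105 = 1.051. At 6 months 2.498 × 1.051 = 2.626, level 0.0087. At 12 months 2.626/1.1 = 2.387, level 0.0170. For r = 1.2 the levels are 0.0058 and 0.0215, and for r = 1.3 they are 0.0038 and 0.0259.

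**Step 4: level with the BIC choice.** Null simulation, 40,000 trials per setting: 80 per arm, 20% missing at 12 months, REML fit with arm-by-time means. The Monte Carlo SE of a level is about 0.0005.

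| ρ | r | BIC keeps unstructured | BIC: 6 / 12 months | Fixed unstructured: 6 / 12 months | Overall error, BIC | Overall error, unstructured |
|---|---|---|---|---|---|---|
| 0.5 | 1.0 | 2% | 0.0123 / 0.0123 | 0.0125 / 0.0128 | 0.044 | 0.045 |
| 0.5 | 1.1 | 22% | 0.0099 / 0.0153 | 0.0119 / 0.0123 | 0.045 | 0.043 |
| 0.5 | 1.15 | 49% | 0.0109 / 0.0152 | 0.0124 / 0.0123 | 0.046 | 0.044 |
| 0.5 | 1.2 | 75% | 0.0123 / 0.0145 | 0.0130 / 0.0127 | 0.048 | 0.046 |
| 0.5 | 1.3 | 98% | 0.0125 / 0.0135 | 0.0126 / 0.0133 | 0.046 | 0.046 |
| 0.7 | 1.0 | 2% | 0.0117 / 0.0126 | 0.0119 / 0.0132 | 0.041 | 0.042 |
| 0.7 | 1.1 | 32% | 0.0107 / 0.0147 | 0.0124 / 0.0121 | 0.043 | 0.042 |
| 0.7 | 1.15 | 66% | 0.0115 / 0.0144 | 0.0122 / 0.0125 | 0.044 | 0.042 |
| 0.7 | 1.2 | 89% | 0.0120 / 0.0128 | 0.0123 / 0.0121 | 0.042 | 0.041 |
| 0.7 | 1.3 | 100% (0.997) | 0.0122 / 0.0123 | 0.0122 / 0.0123 | 0.041 | 0.041 |

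The largest departures are at r = 1.1 and ρ = 0.5: 0.0153/0.0125 = 1.22 at 12 months and 0.0099/0.0125 = 0.79 at 6 months. Fixed unstructured stays between 0.0119 and 0.0133 throughout.

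**The case against.** Several points on the other side stand.

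- **Overall control.** A reader might infer that the guarantee "to ensure that the overall type I error rate across the four tests does not exceed 0.05" is broken. It is not. In every setting the overall error under BIC lies between 0.041 and 0.048, because the four tests are correlated and Bonferroni leaves slack. Always pooling would break the limit when the SDs differ widely (0.0596 at r = 1.3, ρ = 0.5), but there BIC keeps the variances separate in 98% of trials.
- **BIC does not always pool.** A reader might also infer that the rule can only impose equal variances. BIC can keep unstructured, and does so more often as the gap widens. The harm is confined to a middle range.
- **The candidates are assumed.** If every candidate allowed unequal variances, all would be the same model at two times and the choice would have no effect. A candidate list is also something a protocol may leave to the SAP.
- **Selection itself does no harm here.** At equal SDs the levels are nominal although BIC is used, so choosing the structure from the trial data does not by itself inflate the error.
- **The rule has other uses.** With three follow-ups a choice of structure has more content, and those analyses are labelled hypothesis-generating. No benefit was shown from dropping BIC there.

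What remains is that the protocol positively states this rule for the confirmatory model. There it can save only one parameter, and under plausible conditions it misstates both time-specific standard errors.

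**Conclusion.** The point holds as a minor weakness. For the primary QOL model, BIC selection gains at most one parameter. If equal-variance structures are candidates and the residual SDs differ by about 10-20%, the contrasts run at about 0.013-0.015 at the more variable visit and 0.010-0.012 at the other, instead of 0.0125. The drift is absent at equal SDs and almost gone at a ratio of 1.3.

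The documents do not support reading this as a loss of type I error control over the four tests, or as a fault in the models for the other outcomes. The result rests on the assumed SD ratio, correlation and candidate list. Site random intercepts and the other covariates were not simulated, and the 12-month missingness in the simulation did not depend on outcome.

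**What to change.** In section 7.0, Aim 1, limit the BIC sentence to the hypothesis-generating outcomes with three follow-ups. For the primary QOL model, state that the 6- and 12-month scores have an unstructured covariance (two variances and one covariance), with one named fallback used only if that model does not converge. The fallback must be a genuinely different model, because heterogeneous compound symmetry is only a reparameterisation of unstructured at two times.

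The cost is one sentence and one covariance parameter, estimated from up to 240 women (192 with a 12-month score under the planned attrition, 3 × 64). It needs no new data and no change to the sample size.

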## 2.0 Objectives

The study uses a randomized controlled trial (RCT) to test the health benefits of expressive writing that is culturally adapted for Chinese immigrant breast cancer survivors (BCSs). We will recruit Chinese immigrant BCSs (N=240) diagnosed with stage 0-III breast cancer and within 5 years of completion of primary treatment. Recruitment will occur primarily through community-based organizations and from The University of Texas MD Anderson Cancer Center patient database. Participants will be randomly assigned either to a control condition to write about neutral topics or to one of two intervention conditions, self-regulation or self-cultivation, which both aim to promote adaptive cognitive processes but differ in how they achieve this goal. The self-regulation intervention incorporates a traditional Western expressive writing paradigm, whereas the self-cultivation intervention incorporates Asian cultural values. Participants in all three conditions will be asked to write in their preferred language during three 30-minute sessions.

**The primary outcome will be quality of life (QOL)** at the 6 and 12 month follow-ups and the secondary outcomes will be perceived stress, stress biomarkers, and medical appointments for cancer-related morbidities.

**Aim 1:** To determine the health benefits of expressive writing compared with the control condition.

Hypothesis 1.1: Both interventions will improve QOL and reduce perceived stress and medical appointments for cancer-related morbidities at the 6- and 12-month follow-ups.

Hypothesis 1.2: Both interventions will reduce perceived stress and normalize levels of stress biomarkers at the 6-week follow-up.

**Aim 2:** To characterize how acculturation moderates the effects of expressive writing interventions.

Hypothesis 2.1: Those highly acculturated to the dominant American culture will benefit more from the self-regulation intervention and those highly enculturated toward the heritage Asian culture will benefit more from the self-cultivation intervention.

**Aim 3:** To identify mechanisms explaining the benefits of the interventions using mixed methods.

Hypothesis 3.1: Expressive writing will improve posttraumatic growth and relationship harmony and reduce self-stigma, which will in turn improve QOL, investigated using quantitative methods.

Research question 3.2: What culturally specific factors explain the benefits of the interventions, investigated using qualitative methods?

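### The four primary quality-of-life contrasts are each tested at a fixed 0.0125; Holm's step-down would keep the same 0.05 family-wise bound and reject at least as often

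*Protocol*

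**What the plan says.** Section 7.0 defines the primary family in the Aim 1 paragraph: "Hypothesis 1.1 (QOL at 6- and 12-month follow-ups for both intervention conditions) will be tested against the control condition within the LMMs". Two interventions against control at two visits make four contrasts. Each is tested at a "two-sided 0.0125 level of significance, to ensure that the overall type I error rate across the four tests does not exceed 0.05". The power paragraph in the same section uses the same level, "with a Bonferroni adjustment for the four primary comparisons", and sizes the trial per contrast: at least 80% power for a difference of 0.60 SD by a two-sample t-test, with 64 evaluable per group out of 80 randomised. No step-down or other sequential rule is given.

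The protocol expects every one of these effects to be real. Hypothesis 1.1 in section 2.0 reads "Both interventions will improve QOL and reduce perceived stress and medical appointments for cancer-related morbidities at the 6- and 12-month follow-ups". For the second intervention, the power paragraph states "we expect that the self-cultivation intervention condition will have an effect size of 0.6 at the follow-ups".

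**The concern.** The protocol itself fixes the multiplicity method, so this is not a detail left to an analysis plan. The stated aim is only that the overall type I error across the four tests stays within 0.05. A fixed 0.0125 meets that aim, but it holds every contrast to the strictest level even after others have been rejected. Holm meets the same bound without any added assumption and relaxes the level for the remaining contrasts after each rejection.

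At stake is power on individual primary contrasts in a trial that expects several true effects. Validity and sample size are not in question.

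**Working it through.** **Step 1: reproduce the plan.**
- Level: 0.05/4 = 0.0125.
- Power with n = 64 per group, d = 0.60: noncentrality 0.60 × √(64/2) = 3.394, 126 degrees of freedom, two-sided 0.0125. The noncentral t gives 80.35%. With 63 per group it is 79.6%, so 64 is the smallest group size that reaches 80%.
- Attrition: 64/(1 − 0.20) = 80 per group, and 3 × 80 = 240.

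The level, power and sample size all reproduce.

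**Step 2: compare the rules analytically.** Holm tests the ordered p-values against 0.05/4 = 0.0125, 0.05/3 = 0.0167, 0.05/2 = 0.025 and 0.05, and stops at the first failure.
- *It rejects at least as much.* No threshold is below 0.0125, so every contrast with p ≤ 0.0125 is rejected by Holm too.
- *Its error is bounded.* Suppose m of the four nulls are true. At most 4 − m false nulls can be rejected before the first true one, so the first true null to be rejected meets a threshold of at most 0.05/m. The chance that any of the m true nulls has p ≤ 0.05/m is at most m × 0.05/m = 0.05, whatever the dependence.
- *The first step is the same.* Both rules reject something exactly when the smallest p-value is at most 0.0125, so the chance of at least one rejection is identical.

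Single-test power at n = 64, d = 0.60 (noncentral t) at the four thresholds is 80.35%, 83.2%, 86.8% and 92.1%.

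**Step 3: size of the gain.** Simulation of 200,000 trials per scenario, with normal test statistics, 64 per arm and a shared control arm. The protocol gives no correlation between the 6- and 12-month scores, so it is an assumption, varied from 0.3 to 0.9. The normal approximation puts Bonferroni power at 81.5% instead of the exact 80.35%.

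| True effects | Power per contrast, Bonferroni | Power per contrast, Holm |
|---|---|---|
| All four 0.60 SD | 81.5% | 88–89% |
| All four 0.50 SD | 63% | about 72% (71.1% to 72.6%) |
| All four 0.30 SD | 21% | about 25% |
| One arm 0.60 SD, other arm null (effective arm) | 81.5% | about 83% |

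At 0.60 SD for all four, the chance of at least one rejection is 95–99% under both rules. The chance of rejecting all four rises from 54–64% to 76–81%.

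**Step 4: role of the correlation.** At 0.60 SD for all four, Holm's power per contrast falls from 89.4% at correlation 0.3 to about 87.8% at 0.9, and the all-four gain falls from about 22 points (53.7% to 75.9%) to about 16 (64.2% to 80.4%). The gain comes from several effects being real. Holm does not exploit correlation.

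**Step 5: actual family-wise error.** With all four nulls true it is 0.035–0.046, the same for both rules. With one arm null and the other at 0.60 SD it is about 0.02 for Bonferroni and 0.03–0.04 for Holm. All are below 0.05.

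**The case against.** The strongest case against is that nothing here is wrong. The power and Aim 1 paragraphs agree, the error rate is controlled, and the protocol gives a reason for controlling it, namely reproducibility of its main findings. All of that stands, and it is why this is only a suggested improvement.

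Three further objections limit the claim, and each is right:
- *The all-four figure is not a criterion that the protocol sets.* A reader might infer from hypothesis 1.1 that the trial succeeds only if all four contrasts are significant. Section 7.0 does not say so: it tests and powers each contrast separately. If all four were required, no adjustment would be needed, since each could be tested at 0.05 (about 79% power for all four at 0.60 SD and correlation 0.6, against about 78% for Holm). The gain should be judged per contrast.
- *The large gains need large effects in both arms.* The protocol takes 0.60 SD from a 6-month comparison in a preliminary study and carries it to 12 months and to a different intervention. Section 3.0 reports only small effects for the other writing condition in that study. At 0.30 SD the gain is about 4 points.
- *Holm uses more of the error allowance and gives up simple intervals.* Equal error control means the same upper bound, not the same actual rate. Bonferroni tests also match simultaneous 98.75% confidence intervals, whereas a contrast significant by Holm may have a 98.75% interval that includes zero. Preferring the simpler rule for that reason is defensible.

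None of this alters the dominance in step 2, which depends on neither the effect sizes nor the correlation.

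**Conclusion.** The point holds as an inexpensive efficiency improvement. Under the protocol's own assumption of 0.60 SD throughout, Holm adds about 6 to 8 points of power per contrast. At 0.50 SD it adds 8 to 10, at 0.30 SD about 4, and with one null arm about 2. These sizes rest on 64 evaluable per arm, normal test statistics and an assumed visit correlation of 0.3 to 0.9. They do not model the covariate-adjusted mixed model. That Holm rejects at least as often within the 0.05 bound rests on no assumption about dependence.

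A reader might infer more: that the Bonferroni rule is mistaken, that the trial is underpowered, or that correlation among the contrasts is what makes Bonferroni wasteful here. The documents and the calculation support none of these. The rule is valid, the stated power and the 240 participants reproduce, and the gain shrinks as the correlation rises.

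**What to change.** In the Aim 1 paragraph of section 7.0, replace the clause that gives every contrast the fixed 0.0125 level by wording such as: *the four contrasts will be tested by Holm's step-down procedure with a family-wise two-sided level of 0.05, and Holm-adjusted p-values will be reported.* Keep the 0.0125 calculation in the power paragraph, described as a conservative basis. If 98.75% intervals are shown beside the tests, state that the Holm-adjusted p-value governs the decision.

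Make the change before unblinding; afterwards it could look data-driven. It costs one sentence of analysis wording, with no effect on sample size, data collection or participants. The one downside is the possible mismatch between interval and test, which that statement handles.
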